### Eligibility criteria {10}

The following are the inclusion criteria:
Age 18–83 years oldService members with mTBI and civilian patients with vestibular hypofunction, both of which must report vestibular symptoms (i.e., dizziness, imbalance)Visual acuity with correction is ≥ 70 Early Treatment Diabetic Retinopathy Study (ETDRS) letter score (right and left eye)Visual acuity without correction is ≥ 35 ETDRS letter score (right and left eye)Participant has been diagnosed with a mild traumatic brain injury (FBCH site)Participant has been diagnosed with vestibular hypofunction (JHU site)Systolic blood pressure is ≤ 200 mmHg and/or diastolic is ≤ 110 mmHg at rest

The following are the exclusion criteria:
Any person with a self-reported history of significant ophthalmic, neuromuscular, cardiovascular (except hypertension), renal/electrolyte, and Meniere’s diseasePersons with uncontrolled severe hypertension (systolic blood pressure of > 200 mmHg and/or a diastolic blood pressure of > 110 mmHg at rest)Persons with a recent history of alcohol and/or drug abuse within the past 6 monthsPersons with benign paroxysmal positional vertigoCervical spine active range of motion < 45°

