### Sample size {14}

We have based our estimate of sample size on data published in healthy adults (21–58 years old) using the IVE paradigm, whose age reflects our target patient population [30]. In that study, active VOR gain pre-adaptation was 0.92 ± 0.18 and active VOR gain post adaptation was 1.11 ± 0.22. Therefore, using the mean difference between pre- and post-adaptation of 0.19 with a standard deviation of 0.18, we would need a minimum of 9 participants to be able to reject the null hypothesis with a probability (power) of 0.8, presuming *α* < 0.05 (PS Power and Sample Size Calculations, version 3.1.2). Presuming a 25% attrition, we will recruit at least 12 participants for each of the IVE-VPT and VPT-IVE patient cohorts (aims). We aim to enrol 24 service members at the FBCH site and 24 civilians at the JHU Outpatient Center for each of aims I–III.

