## Statistical methods

### Statistical methods for primary and secondary outcomes {20a}

The primary outcome for determining treatment efficacy is VOR gain, which is measured weekly for each subject in each intervention period. To verify randomization between sequences, baseline demographics and characteristics of vestibular injury will be compared across arms. The primary analysis will follow the intent to treat principle, where patient outcomes are analyzed following how they were randomized and not adjusted or excluded based on adherence to assigned treatment. To determine the efficacy for the primary outcome, a generalized linear mixed model will be used with VOR gain as the dependent factor [31]. This model will be used to compare VOR gain between interventions and to estimate period and carryover effects. With substantial washout periods for each aim, we do not expect there to be substantial differences in the carryover effects between intervention sequences. We will verify there are no differences in the carryover effects by testing for an interaction between treatment and time. If this interaction is statistically significant at *α =* 0.05, we will focus our analysis on patient outcomes in the first period, and disregard outcomes in the following period. We will adjust this model for site as well as demographic and vestibular injury-related factors that are imbalanced between arms at baseline. All statistical tests will be conducted as two-sided for an *α* of 0.05.

For secondary analyses, we will examine the compensatory saccade metrics, which are also measured at each weekly visit similarly to VOR gain. Similar to our analysis of the primary outcome, we will examine this secondary outcome with a generalized linear mixed model, estimating carryover effects by testing for an interaction between period and intervention. We will also adjust these comparisons of VOR gain and compensatory saccade metrics for site and for factors that are imbalanced at baseline. Analyses with greater than 25% loss to follow-up or incompleteness for other reasons will use multiple imputation [31]. All analyses will be conducted using the SAS software version 9.4 (SAS Institute Inc., Cary, NC, USA).

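### Covariates beyond site enter the VOR gain model only if imbalanced at baseline, so enrolment VOR gain may be left out; the cost falls mainly on the first-period fallback analysis

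*Protocol article*

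**What the plan says.** The section Statistical methods for primary and secondary outcomes {20a} states the outcome ("The primary outcome for determining treatment efficacy is VOR gain, which is measured weekly for each subject in each intervention period") and the model ("a generalized linear mixed model will be used with VOR gain as the dependent factor"). It then sets a two-step covariate rule.

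- Step one is a baseline comparison: "To verify randomization between sequences, baseline demographics and characteristics of vestibular injury will be compared across arms".
- Step two uses its result: "We will adjust this model for site as well as demographic and vestibular injury-related factors that are imbalanced between arms at baseline". The rule is repeated with the secondary analyses: "We will also adjust these comparisons of VOR gain and compensatory saccade metrics for site and for factors that are imbalanced at baseline".

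Site is the only covariate named in advance. No list of candidate factors and no definition of imbalance is given. The same section says that a significant carryover test leads to an analysis of the first period alone.

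Four other places bear on this:

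- Sequence generation {16a} and Concealment mechanism {16b} describe a computer-generated schedule stratified by clinical center and released centrally.
- Table 1 lists the video head impulse test in the one-time characterization at enrollment, and again weekly in each treatment period (weeks 1–6 and 13–18 in aim I).
- Study setting {9} and Eligibility criteria {10} place all mTBI participants at FBCH and all participants with vestibular hypofunction at JHU.
- Sample size {14} says: "We aim to enrol 24 service members at the FBCH site and 24 civilians at the JHU Outpatient Center for each of aims I–III".

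**The concern.** With concealed random allocation, a baseline difference between sequences is a chance event. It says nothing about whether a factor predicts the outcome, and prediction is what makes adjustment worthwhile. A rule driven by imbalance therefore makes the fitted model depend on the data and can leave out a strongly prognostic variable that happens to be balanced.

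The variable at stake is VOR gain at enrolment, the baseline value of the primary outcome. If it counts as a vestibular injury-related factor, it enters only when imbalanced. If it does not count, the rule never brings it in. Either way its inclusion is not guaranteed, although it is already collected.

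What this costs depends on the analysis. A within-person contrast removes stable differences between people without a covariate. A first-period comparison is between people, and there a baseline value of the outcome can remove much of the variance.

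**Working it through.** **The plan's own figure.** Sample size {14} uses a mean change of 0.19, SD 0.18, power 0.80 and α 0.05, and states 9 participants, or 12 after 25% attrition. As a paired t-test, n = 9 gives power 0.792 and n = 10 gives 0.843, and 9/0.75 = 12. The figure reproduces, but it is a pre-post calculation and does not test the covariate rule.

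**Inputs for the check**

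- From the protocol: 24 + 24 enrolled per aim, 25% attrition, 1:1 allocation, two-sided α 0.05. Completers are 48 × 0.75 = 36, or 18 per sequence.
- Assumed: both sites pooled, one VOR gain value per person, between-person SD 0.20, correlation ρ of 0.5, 0.7 or 0.8 between baseline and outcome, and imbalance meaning p<0.05 on a two-sample t-test.

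**Complete crossover.** Take 0.18 as the SD of the within-person difference (assumed; within-person SD 0.18/√2 = 0.127).

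- SE = ½ × 0.18 × √(2/18) = 0.030.
- Simulated mean SE was 0.0297 without a person-level baseline covariate and 0.0301 with it. There is nothing to gain here.

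**First-period comparison**

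- Without baseline gain: SE = 0.20 × √(2/18) = 0.0667.
- With baseline gain: SE = 0.0667 × √(1 − ρ²) = 0.0577, 0.0476 and 0.0400 for ρ = 0.5, 0.7 and 0.8.
- Hand check for a difference of 0.12, using Φ(0.12/SE − 1.96): about 0.44 unadjusted, and 0.55, 0.71 and 0.85 adjusted.

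Under randomization, baseline gain is flagged at p<0.05 in only about 5% of trials. The rule therefore fits the unadjusted model about 95% of the time. Simulation (least squares with site in the model, 6,000 runs per setting) gave these rejection rates:

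| ρ | True difference | Imbalance rule | Always adjusted |
|---|---|---|---|
| 0.5 | 0 | 0.041 | 0.052 |
| 0.7 | 0 | 0.039 | 0.050 |
| 0.8 | 0 | 0.031 | 0.049 |
| 0.5 | 0.12 | 0.411 | 0.511 |
| 0.7 | 0.12 | 0.419 | 0.680 |
| 0.8 | 0.12 | 0.439 | 0.829 |
| 0.5 | 0.19 | 0.794 | 0.882 |
| 0.7 | 0.19 | 0.806 | 0.965 |
| 0.8 | 0.19 | 0.805 | 0.995 |

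With no adjustment at all, power at 0.12 was 0.411, 0.413 and 0.424. The rule recovers almost none of the available precision, and it makes the test slightly conservative.

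**By-site reporting.** With 0.18 again as the assumed SD of the within-person difference, the smallest between-site difference in effect detectable with 80% power is (1.96 + 0.842) × 0.18 × √(2/n). This is 0.168 with 18 completers per site and 0.146 with 24. Only differences nearly as large as the planning effect of 0.19 would be found.

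**The case against.** The best defence is that the primary analysis is the two-period crossover, where the choice of person-level covariates hardly affects the treatment standard error. That stands. The loss arises mainly in a fallback that is used only if the carryover test is significant: about one time in twenty by chance, more often if there is real carryover. Type I error is not inflated either; it drops to 0.031–0.041.

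It could also be said that covariates belong in an SAP. That does not answer the point, because the protocol does not leave the choice open. It states a selection rule, twice.

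A reader might infer more than the text supports:

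- *A 40% to 64% chance that some factor is flagged.* This is 1 − 0.95^10 to 1 − 0.95^20. It needs a 0.05 threshold, 10 to 20 factors and independence among them, none of which the protocol states. It also does not show how far the treatment estimate would move.
- *A baseline-outcome correlation of 0.61.* This is 0.0484/0.0792, solved from SDs of 0.18 and 0.22, and it holds only if 0.18 is the SD of the change. The protocol does not say so, and 0.18 is also its pre-adaptation SD. The data are active VOR gain in healthy adults, not vHIT gain in patients. Hence the range used above.
- *One common effect is imposed on two diseases.* The protocol says the model is adjusted for site. It does not say that an interaction is excluded, and an SAP could add one. Methods for additional analyses {20b} points back to a section that describes no subgroup analysis, but that is thin evidence in a condensed article. A pooled estimate is also a valid average over the enrolled population, and the Background gives a reason for pooling: inner-ear damage is common whatever the cause.

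**Conclusion.** The point holds in a limited form. The stated rule makes the VOR gain model depend on chance imbalance and does not secure adjustment for the baseline value of the primary outcome.

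The effect on the complete crossover estimate is negligible. In the first-period analysis, for a true difference of 0.12, the rule gives up about 10, 26 and 39 percentage points of power at correlations 0.5, 0.7 and 0.8. At 0.19 the loss is about 9, 16 and 19 points. These sizes rest on the assumed SD of 0.20, the assumed correlations, 36 completers and a p<0.05 definition of imbalance. That enrolment VOR gain is the strongest prognostic factor is a reasonable expectation, not something the protocol shows.

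The coincidence of site with diagnosis supports reporting results by site. It does not support a claim that the plan's model is wrong on this account.

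**What to change.** In section {20a}, replace the covariate sentence and its repeat under the secondary analyses with a rule fixed in advance. For example:

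> Each model will include site, as the randomization stratum, and the enrolment value of the outcome analysed (VOR gain for the primary model). Covariates will not be chosen by observed imbalance. Baseline characteristics will be presented descriptively by sequence.

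Use the same set in the first-period analysis. Do not use the week 1 or second-period first-visit vHIT value (week 13 in aim I) as a covariate while it is also part of the weekly outcome series. The second-period value is also post-randomization and may carry first-period effects.

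Add that the IVE-VPT difference will be given with a confidence interval for each site beside the pooled estimate. Label it descriptive, note the low power for an interaction, and note that diagnosis cannot be separated from centre in this design.

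The cost is wording. The variables are already scheduled, adjusting for one baseline value uses one degree of freedom, and the by-site intervals will be wider than the pooled one.

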### Interim analyses {21b}

No interim analyses are planned for the INVENT VPT Trial.

### Methods for additional analyses (e.g., subgroup analyses) {20b}

This is addressed in the “Statistical methods for primary and secondary outcomes {20a}” section.

### Methods in analysis to handle protocol non-adherence and any statistical methods to handle missing data {20c}

This is addressed in the statistical methods section.

### Plans to give access to the full protocol, participant-level data, and statistical code {31c}

Investigators engaged in the Department of Defense-sponsored research must share participant-level data and the study protocol to the Federal Interagency Traumatic Brain Injury Research Informatics System (FITBIR). De-identified INVENT VPT data will also be available upon request to the principal investigator.

### Oversight and monitoring

#### Composition of the coordinating center and trial steering committee {5d}

The INVENT VPT Data Coordinating Center (DCC) is responsible for assuring that the proposed study design and methods are statistically sound, that the investigators and study personnel adhere to the protocol, that valid and reliable data are collected and integrated, and that the accumulated data are summarized and reported as required to monitor study progress and promote and assess data quality. The DCC is composed of a director, data programmer, and biostatistician. A trial steering committee has not been formed for this trial.

Specific tasks are given by phase of the INVENT VPT Trial. Some of the operations at the DCC are designed to facilitate operations at the clinical centers.

#### Initial design phase

DCC responsibilities during this period are as follows:
To assist with the development of the study design and to estimate sample size requirementsTo outline the data collection methods, data management methods and operations, and plans for data reportingTo outline quality assurance and monitoring proceduresTo draft, critique, and revise major portions of the manual of procedures and assure adherence to the protocolTo evaluate currently available hardware and software for data collection, management, and analysisTo design the training session for the INVENT VPT

#### Protocol refinement and implementation phase

This phase begins when funding is awarded and ends when patient enrollment is initiated or shortly thereafter. DCC responsibilities during this period are as follows:
To test and refine data collection methods in REDCapTo complete assigned portions of the manual of procedures and edit for consistency and ease of referenceTo implement the central data management system and test procedures and operations, including tasks such as acquisition, installation, and implementation of necessary hardware and software; writing data definition tables; and editing of tables for data items to be collectedTo develop materials for training and certifying clinical center staff in INVENT proceduresTo design aids to assist with the management of all INVENT centers, including reports to clinical centersTo update INVENT data collection forms and distribute electronic copies to the clinical centersTo undertake site initiation visits and to ensure timely startup

#### Enrollment and follow-up phases

The following are the data management responsibilities:
To receive clinical data from INVENT VPT clinical center staff via REDCapTo edit all data for completeness, accuracy, and consistency and to resolve anomalous data with clinical center staffTo revise data entry screens as requiredTo prepare periodic reports concerning enrollments, completeness of scheduled follow-up interviews, and database quality

The following are the data analysis and reporting responsibilities:
To employ appropriate statistical methods for analysis and summarization of accumulated data based on the recommendations of the study biostatisticianTo undertake the final data analyses for INVENT VPT primary manuscriptsTo maintain the data files in a secure manner to assure their integrityTo back up data files to assure that data are not lostTo maintain a program of regular monitoring of the quality of the INVENT VPT database

#### Composition of the data monitoring committee, its role, and reporting structure {21a}

The interventions included in the INVENT VPT are considered minimal risk so a data monitoring committee will not be included in this trial. An independent medical monitor will review all adverse events that are reported during the conduct of the INVENT VPT Trial and assess the potential that the event may be attributed to the study interventions or participation in the trial. The medical monitor’s findings will be reported to the IRB.

#### Adverse event reporting and harms {22}

Some of the tests may cause symptoms of neck pain, dizziness, nausea, and/or motion sickness. The participant will be asked to report any of these symptoms to the investigator. The participant or the investigator may stop testing at any time. These symptoms usually resolve once testing has stopped. Infrequently, motion sickness symptoms may persist for as long as a few hours.

To minimize the risk of neck strain, severe neck pain, or other cervical injuries due to head-on-body movements, all such movements are first self-generated by the participants. Passively received (i.e., delivered by the experimenter) head movements are kept within the participant’s demonstrated range of self-generated head movements. In keeping with standard clinical practice, participants with known cervical spine instability are not subjected to tests requiring rapid head-on-body movements. To minimize the risk of skin irritation, the skin of the neck will be examined for irritation before we apply electrodes for vestibular evoked myogenic potential testing.

Balance and gait testing have a small risk of falling. To ensure that participants do not fall, testing is conducted with investigators or clinical support staff placed around them to assist as needed. Medical risks, listing all procedures, their major and minor risks, and expected frequency are always conveyed to the participants.

Any adverse events will be recorded on an adverse event form and reported within 24 h to the principal investigator. The principal investigator will notify the IRB by the next business day.

#### Frequency and plans for auditing trial conduct {23}

Onsite and remote data monitoring will be completed via an export of key data from the RedCap database. Data monitoring of key data points will be completed by the DCC. The responsibilities for remote data monitoring at the DCC are as follows:
To develop and test a SAS program to monitor incoming data for inconsistencies based on cross form, within form, cross visit, range, consistency, and expected data entry checksTo execute the SAS program that monitors incoming data for inconsistencies on a weekly basis during data collectionTo distribute data quality queries to Clinical Coordinators biweekly

Data entered into the REDCap system by the Clinical Centers will also be monitored for out-of-range values, inconsistent data, and double data entry inconsistency and completeness.

Periodic in-person site visits are necessary to ensure that there is standardization of procedures, that personnel have been trained adequately, that the clinical facilities meet standards, and that participants and their data are being managed as specified in the protocol. A standard agenda is used for monitoring visits. All sites are visited within the first 3 months of the initiation of participant recruitment and then again at 6 months after the commencement of participant recruitment. Other clinical center monitoring visits shall be conducted on an as-needed basis.

General areas of review during the site visit include the following:
Clinic staff, facilities, and equipmentFlow of participants through the clinicUp-to-date study documentation including the manual of procedures, data collection forms, and documentation confirming reports of serious adverse events to the local IRB and other regulatory documentsReview of signed consent forms for 100% of participantsReview of a sample (approximately 10%) of data collection forms for comparison with data in the REDCap database and source documentsObservation of the study coordinator during a participant visit, if possibleStorage and access to study participant files, including proper storage of signed consent forms and handling of data quality queriesDiscussion of individual participants with compliance problems that may be alleviated by the study coordinator or other study personnelMeeting with the principal investigator of the clinic to discuss any areas of concern

The PI, study coordinator, and site co-investigators receive a detailed report of the findings within 7 business days. Recommendations for remedial actions with a timeline for resolution are included, if necessary. The monitor will also inform the study PI of any remedial actions recommended within 7 business days of the site visit and will submit a subsequent report to the PI summarizing resolution of all deficiencies within 14 business days of final resolution by the clinical center. Remote monitoring will be independent from the study investigators and the Department of Defense.

#### Plans for communicating important protocol amendments to relevant parties (e.g., trial participants, ethical committees) {25}

Protocol amendments, including any modifications to the eligibility criteria, study design, recruitment procedures, or analysis plan will be documented in a revised protocol with a new version number and date. These modifications will be submitted to the IRB and approved prior to distribution to the clinical centers. All protocol modifications, including those that do not significantly impact the conduct of the study, will be communicated to the INVENT VPT investigators and personnel via a policy and procedures memorandum.

#### Dissemination plans {31a}

It is expected that the PI of the INVENT VPT Trial will be responsible for the dissemination of the INVENT study methods and findings in appropriate locations of visibility (talks, journals). As the data collection develops and statistics are applied, it will be the PI’s responsibility to discuss authorship and order of authorship with the appropriate study team members. It is likely that many of the eventual manuscripts will include references to the INVENT VPT study team participants, rather than listing each individual as an author. Ultimately, a decision on authorship will be made via study team discussion and the final decision by the PI.

